### Randomization

Participants will be randomized to our three web-based interventions in a factorial design (see overview of study design and Table 2). Postgraduates and faculty MDs will be randomized separately and further stratified according to time since last search (<= 365 days vs. >365 days; see Table 5), as an overall proxy of their baseline frequency searches in MacPLUS FS. Right before the beginning of the trials, participants will be randomly allocated to each factorial group (2^3^ = 8 groups), balancing on blocks of 16 within each stratum (=2 - 8). Our information technology programmers, in charge of MacPLUS FS system administration, will perform randomization using a computer-based pseudo-random number generator. They will maintain a secure master list of the randomization codes and assignments, and conceal allocation from the analysts.

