Finally, we will explore if the interventions modify the patterns of use of the different EBM resources, and in particular if they increase the accesses to higher levels of evidence, such as summaries and pre-appraised research, compared to non-pre-appraised research. Table 6 displays the baseline distribution of access across the pyramid of EBM resources among clinicians that have adopted MacPLUS FS, that is, `regular-searchers’ and `super-searchers.’ With 1,025 searches, these users have conducted about 75% of all searches in MacPLUS FS, and accessed one of its resources 1,390 times in total. All resources in the federated search were consulted: summaries were accessed 53.2% of the times, pre-appraised research in 16.1%, and non-pre-appraised research in 30.6% of the times. Postgraduates searched less summaries than faculty did (49.0% vs. 63.8%), and more non-pre-appraised resources (35.3% vs. 19.3%).

**Table 6 Tab6:** **Baseline frequency of access to EBM resources (% of all accesses), among `regular-searchers’ and `super-searchers’***

		Postgraduates	Faculty	Total
		(n = 53)	(n = 28)	(n = 81)
		739 searches	286 searches	1,025 searches
**Summaries**		**485 (49.0%)**	**255 (63.8%)**	**740 (53.2%)**
	DynaMed	174 (17.6%)	39 (9.8%)	213 (15.3%)
	UpToDate	120 (12.1%)	128 (32.0%)	248 (17.8%)
	Best Practice	147 (14.8%)	71 (17.8%)	218 (15.7%)
	ACP PIER	44 (4.4%)	17 (4.3%)	61 (4.4%)
**Pre-appraised research**		**156 (15.8%)**	**68 (17.0%)**	**224 (16.1%)**
	Synopses of systematic reviews	23 (2.3%)	17 (4.3%)	40 (2.9%)
	Systematic reviews	66 (6.7%)	21 (5.3%)	87 (6.3%)
	Synopses of studies	10 (1.0%)	4 (1.0%)	14 (1.0%)
	Studies	57 (5.8%)	26 (6.5%)	83 (6.0%)
**Non-pre-appraised research**		**349 (35.3%)**	**77 (19.3%)**	**426 (30.6%)**
	Filtered studies	257 (26.0%)	60 (15.0%)	317 (22.8%)
	Unfiltered studies	92 (9.3%)	17 (4.3%)	109 (7.8%)
**Total number of accesses**		**990 (100%)**	**400 (100%)**	**1,390 (100%)**

**i.e*., clinicians who conducted more than one search per month on average.

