### Hypotheses and statistical analysis

The two trials are separate and will be analyzed as such. We have three primary hypotheses for each trial: that the clinical question recorder will be more effective than the control; that the evidence retrieval coach will be more effective than the control; and that audit, feedback and gamification will be more effective than the control. Each of these hypotheses will be tested separately (half of the sample compared to the other half). The effect of each intervention will be tested by regressing the average number of searches per month over the trial’s six-month time period for each user onto dummy variables for each intervention, controlling for search frequency at baseline. The distribution of the number of searches per user is not known at present, but baseline data suggests excess zeros with extra-Poisson variation. We will attempt to capture the distribution parametrically, but in the event that it is not possible to do this accurately, we will use ordinary least squares to estimate the regression coefficients together with heteroscedasticity-robust standard errors.

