### Power calculation

Since we anticipated that interactions among the interventions are unlikely, we have powered the trials assuming no such interactions. Before the trials began, we had 904 participants eligible for the study, of whom 429 were postgraduates and 475 were faculty (see Table 5). Baseline data indicated a mean of 0.46 searches per month per user (SD 1.42) among postgraduates and 0.20 searches per month per used (SD 0.83) among faculty. Additional file 4 shows power curves for the faculty and for the postgraduates. These indicate that among the postgraduates, we will have 80% power to detect an increase of 0.9 in the mean number of searches per month, and among the faculty we will have 80% power to detect an increase of 0.5 in the mean number of searches per month.

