### Analysis of secondary questions

An exploratory analysis will investigate time trends in intervention efficacy. Rather than using the average number of searches per user per month over the six months of the trial, we will conduct a longitudinal analysis using the number of searches per user for each of the six months of the trial as the dependent variable, regressed onto time, dummy variables for each of the interventions, the interaction between time and intervention, together with search frequency at baseline. This regression model will be fitted using a Generalized Estimating Equation (GEE).

Finally, we will compare the distribution of answers on the IAM questionnaire *(i.e*., utility, use and usefulness of the evidence retrieved), as well as the distribution of access to the different EBM resources, using chi-squared tests.

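### The chi-squared test on resource accesses ignores clustering within the randomised user, so it rejects too often, by an amount that depends on a within-user correlation the protocol does not give

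*Protocol article*

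**What the plan says.** Under Analysis of secondary questions, the protocol article names the method for the IAM answers "as well as the distribution of access to the different EBM resources, using chi-squared tests". It states no adjustment for the user. The paragraph just before uses GEE for repeated monthly search counts, so within-user correlation is dealt with there but not for accesses.

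The distribution meant is described under Secondary outcomes and questions. Table 6 is titled "Baseline frequency of access to EBM resources (% of all accesses", and the text says that regular- and super-searchers "accessed one of its resources 1,390 times in total". The three pyramid levels are reported in the same unit: "summaries were accessed 53.2% of the times, pre-appraised research in 16.1%, and non-pre-appraised research in 30.6% of the times".

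Under Randomization, "participants will be randomly allocated to each factorial group". Under Hypotheses and statistical analysis, the postgraduate and faculty trials are to be analysed separately, and each primary hypothesis compares the two halves of the sample: "half of the sample compared to the other half". I assume the same contrast for accesses.

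**The concern.** Pearson's chi-squared test requires independent observations. Here the observations are accesses, nested in the users who were randomised.

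The protocol itself gives reasons to expect correlation within a user:
- The Background lists reliance on a single favourite resource as a known barrier to wider searching.
- The note to Table 1 says that remote access to full text can depend on a user's own subscriptions.
- Table 6 shows 1,390 accesses from 1,025 searches (1,390/1,025 = 1.36 per search), so accesses also cluster within searches.

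Use is concentrated as well. A super-searcher exceeds five searches a month, which is more than 30 in six months if registered throughout. On that basis the eight postgraduate super-searchers made more than 240 of 739 searches (32%), and the four faculty super-searchers more than 120 of 286 (42%). Stratification is by whether the last search fell within 365 days, which does not balance these users across arms. If each allocation is treated as a coin toss, four users split 3:1 or 4:0 with probability 1 − 6/16 = 63%.

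At stake is the comparison that would show whether an intervention shifts use towards summaries and pre-appraised research. A few heavy users with settled habits, falling by chance into one arm, could produce a significant but spurious shift.

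**Working it through.** **Reproducing Table 6.** Postgraduates: 485 + 156 + 349 = 990. Faculty: 255 + 68 + 77 = 400. Total: 740 + 224 + 426 = 1,390, which gives 53.2%, 16.1% and 30.6% as printed.

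**Accesses per user.** Postgraduates: 990/53 = 18.7. Faculty: 400/28 = 14.3. Because the trials are analysed separately, these are the relevant figures, not the pooled 81 users.

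**Allowing for unequal use.** The Power calculation gives "0.46 searches per month per user (SD 1.42) among postgraduates" and, for faculty, a mean of 0.20 with SD 0.83. The size-weighted mean number of searches per user over six months is 36 × [(n − 1)SD² + n × mean²] / (6 × n × mean).
- Postgraduates: 36 × (428 × 1.42² + 429 × 0.46²) / (6 × 429 × 0.46) = 29.0. At 990/739 = 1.34 accesses per search, this is about 39 accesses.
- Faculty: 36 × (474 × 0.83² + 475 × 0.20²) / (6 × 475 × 0.20) = 21.8. At 400/286 = 1.40 accesses per search, this is about 31 accesses.

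These are upper-end approximations. They use the stated means, which exceed total searches divided by users and months (935/429/6 = 0.36; 423/475/6 = 0.15).

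**Formula.** Design effect DE = 1 + (m − 1) × ICC. With three pyramid levels and two arms the test has 2 degrees of freedom, so the actual level of a nominal 5% test is P(χ²₂ > 5.991/DE) = 0.05^(1/DE). Example for postgraduates at ICC 0.05 with equal use: DE = 1 + 17.68 × 0.05 = 1.88, and 0.05^(1/1.88) = 20%.

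**Simulation.** Dirichlet-multinomial accesses with no intervention effect; 53 and 28 users split 1:1; skewed user sizes built to agree with Tables 5 and 6; Pearson chi-squared on the 2 × 3 table of accesses; 4,000 runs per setting. Size-weighted means were 30.5 and 23.4 accesses, between the equal and skewed cases above. Simulated faculty accesses averaged 410 rather than 400. Repeat runs agreed within about two percentage points; the ranges cover them.

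| ICC (assumed) | Postgraduates: formula, equal / skewed use | Postgraduates: simulated | Faculty: formula, equal / skewed use | Faculty: simulated |
|---|---|---|---|---|
| 0 | 5% / 5% | 5% | 5% / 5% | 5% |
| 0.01 | 8% / 11% | 9–10% | 7% / 10% | 7–8% |
| 0.02 | 11% / 18% | 15% | 9% / 15% | 11–12% |
| 0.05 | 20% / 36% | 30–31% | 17% / 30% | 23–24% |
| 0.10 | 34% / 54% | 44–45% | 28% / 47% | 36–37% |
| 0.20 | 52% / 71% | 63–65% | 44% / 65% | 56–57% |

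The first row shows that the test keeps its level when accesses really are independent. The excess in the other rows is due to clustering.

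**The case against.** The strongest case on the other side is that this is an exploratory secondary question in a study the authors liken to a phase II trial. No primary hypothesis or power figure depends on it. Further, the protocol does not say outright that the test is run on pooled accesses, and a fuller analysis plan might add a correction. The first part stands and limits the severity. The second does not remove the point: the article names the test, and its only description of the distribution is in accesses.

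Several stronger readings are tempting but not supported:
- *Thousands of accesses from a handful of users.* Baseline shows 990 and 400 in the two trials. Counts during the trial are unknown.
- *A false-positive rate certain to be several times nominal.* That depends on an ICC the protocol does not give. At 0.01 the simulated rate is at most double the nominal rate.
- *The trial's only test of search quality.* The IAM outcomes (utility, use, usefulness) also bear on quality. This is the only planned test of movement across the pyramid.
- *The IAM comparison shares the fault because it shares the sentence.* It does not, since invitations stop once a user has returned one completed questionnaire on a clinical question.
- *The analysis is invalid because it is limited to people who search.* The restriction to regular- and super-searchers describes the baseline table and is not stated for the trial analysis. Any analysis of shares conditions on having accesses, including the clustered models proposed below, so this concerns interpretation rather than the test.

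**Conclusion.** The point holds in a limited form. As written, the chi-squared test on accesses ignores the randomised unit and is anti-conservative. I am confident of the direction, but the size is conditional. With an assumed two-sided 5% level, baseline volumes and three pyramid levels, the simulated false-positive rate runs from about 7–10% at an ICC of 0.01 to about 56–65% at 0.20. It reaches roughly five times nominal at 0.05. An ICC of that order is plausible if clinicians favour one resource, but it is an assumption.

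The consequence is confined to the exploratory claim about use of the evidence pyramid. The primary analysis regresses one value per user and is unaffected. This is a should-fix.

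**What to change.** Within each trial, replace the plain chi-squared test on accesses with one of the following:
- a multinomial (or binomial) model for the pyramid level, with the three intervention dummies and standard errors clustered on user;
- a Rao-Scott-corrected chi-squared test;
- a permutation test that reassigns whole users, for one intervention at a time, within randomisation strata and within combinations of the other two interventions.

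With as few users as the 28 faculty at baseline, and a few of them dominating, I would favour the permutation test or use it as a check, because clustered standard errors can be unreliable in that setting.

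Optionally, report per-user access counts at each pyramid level for all randomised users. This avoids conditioning on having searched, but it mixes level with total search volume, so it complements the analysis of shares and does not replace it.

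The cost is one sentence in the analysis section. Use is already recorded by individual account, so no new data are needed. P-values will be less favourable than those from the plain test.

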### Outcomes

#### Primary outcome

Our primary question is whether each intervention increases the quantity of searches to answer questions - *i.e*., search utilization (not counting logins to e-mail alerts or to access other resources). This will be measured by (i) rate of searches/month/user, (ii) and corresponding proportions of `super-searchers’ (>five searches/month), `regular-searchers’ (one to five searches/month), `occasional-searchers’ (<one search/month), and `alert-only-users’ (no searches/month). The primary outcome will be averaged over six months, but continuously recorded as participants will be signed on through their individual user account that tracks logins and use of EBM resources, down to individual keystrokes.

Table 5 shows the baseline utilization data during the six months prior to the start of the trial, from July to December 2013. Postgraduates MDs (n = 429) searched MacPLUS FS 935 times in total, corresponding to about 0.46 searches/month/user, whereas they accessed 4,064 alerts to new evidence, corresponding to 1.65 alerts/month/user, and consulted other web-resources in MacPLUS FS 0.52 times/month/user. About 66.9% of postgrads users were `alert-only-users,’ while 10.5% were `regular-searchers’ and 1.9% `super-searchers.’

The utilization patterns were different for Faculty MDs (n = 475) who searched MacPLUS FS half as much, about 423 times in total, corresponding to about 0.20 searches/month/user, whereas they accessed almost twice as many alerts to new evidence, 7,092 alerts in total, corresponding to 2.54 alerts/month/user, and consulted other web-resources in MacPLUS FS 0.32 times/month/user. About 78.9% of faculty used were `alert-only-users,’ while 5.1% were `regular-searchers’ and 0.8% `super-searchers.’

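### The chi-squared test planned for access to EBM resources cannot use users' logged baseline accesses and, if accesses are the unit counted, treats one user's repeated accesses as independent

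*Protocol article*

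**What the plan says.** The section Secondary outcomes and questions poses the question: "Finally, we will explore if the interventions modify the patterns of use of the different EBM resources", in particular whether access moves toward summaries and pre-appraised research. Analysis of secondary questions fixes the method in one clause: the questionnaire answers are compared, "as well as the distribution of access to the different EBM resources, using chi-squared tests". It names no baseline term, unit of counting or allowance for repeated accesses.

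The other log-based analyses with a stated method do use baseline. The primary regression (Hypotheses and statistical analysis) is run "controlling for search frequency at baseline". The GEE for time trends includes "the interaction between time and intervention, together with search frequency at baseline".

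The material for a baseline term exists. Under Primary outcome, participants are signed on through an "individual user account that tracks logins and use of EBM resources, down to individual keystrokes". "Table 6 displays the baseline distribution of access across the pyramid of EBM resources among clinicians that have adopted MacPLUS FS", namely the regular- and super-searchers. The text adds: "With 1,025 searches, these users have conducted about 75% of all searches in MacPLUS FS", and that they "accessed one of its resources 1,390 times in total". The Randomization section stratifies, within each trial, only by whether the last search was more than 365 days ago.

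**The concern.** The question is whether an intervention changes which layers of evidence a user opens. Layer preference is plausibly a personal habit, and a small group supplies most of the activity. Two consequences follow.

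First, a chi-squared table has no covariate, so it cannot separate a change in pattern from a pattern that a user already had.

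Second, if each access is one count in the table, one heavy user contributes many correlated counts and the test understates the true error. Stratifying by time since last search balances neither heavy use nor layer preference, so chance placement of a few heavy users can look like an effect.

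At stake is the log-based evidence on the quality of searching. The other source is the impact questionnaire, for which the Discussion itself expects that response may be poor.

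**Working it through.** **1. The plan's own figures (Tables 5 and 6) reproduce.**
- Shares of the 1,390 accesses: summaries 740/1,390 = 53.2%, pre-appraised 224/1,390 = 16.1%, non-pre-appraised 426/1,390 = 30.6%.
- Searches by the 81 regular- and super-searchers: 1,025/1,358 = 75.5%. Postgraduates: 53 users made 739/935 = 79%. Faculty: 28 users made 286/423 = 68%.
- 81/904 = 9.0% of users; 12 of them are super-searchers.

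**2. Clustering, by formula.** Accesses per user in Table 6: 990/53 = 18.7 (postgraduates) and 400/28 = 14.3 (faculty). With equal clusters, the design effect is 1 + (m - 1) x ICC. The true rejection rate of a nominal 5% test with one degree of freedom is then P(|Z| > 1.96/√deff). The ICC is not in the documents, so a range is shown.

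| ICC (assumed) | Postgraduates: deff, rejection | Faculty: deff, rejection |
|---|---|---|
| 0.05 | 1.88, 15% | 1.66, 13% |
| 0.10 | 2.77, 24% | 2.33, 20% |
| 0.20 | 4.54, 36% | 3.66, 31% |
| 0.30 | 6.30, 44% | 4.99, 38% |

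Unequal clusters, which a few super-searchers create, make this worse.

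**3. Clustering, by simulation with no true effect** (2,000 runs per setting, Table 6 numbers of users and accesses, summaries versus the rest). Assumptions not in the documents: two-sided alpha 0.05, super-searchers make 45% of accesses, between-user SD on the logit scale 0.5 to 1.5 (ICC about 0.07 to 0.41).
- Chi-squared on pooled accesses: rejection in about 25% to 59% of runs for postgraduates; about 41-42% for faculty at logit SD 1.0.
- If users do not differ at all (logit SD 0): 4.4%, so the excess comes wholly from differences between users.
- User-level regression weighted by accesses, with the baseline share and leverage-corrected robust errors: about 4.5% to 6%.
- A second simulation (53 postgraduates, about 990 accesses, logit SD 1.0) used baseline log-counts as covariates. The pooled chi-squared rejected in about 41-45% of runs, a plain binomial model with those covariates in 22-40%, and user-level robust errors in about 8-11%.

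The baseline covariate alone therefore does not cure the error rate. Robust errors do most of the work, and with about 50 users or fewer they need care.

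**4. Chance imbalance.** With independent accesses split evenly, the SD of the difference in the summaries share is √(p(1-p) x 4/N): √(0.49 x 0.51 x 4/990) = 3.2 points for postgraduates and √(0.638 x 0.362 x 4/400) = 4.8 points for faculty. At logit SD 1.0 the simulated SD of the baseline difference between halves is about 8.5 and 11.5 points.

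**5. Precision gained from the baseline term.**
- First simulation, postgraduates: variance falls by 4-9% at within-user correlation 0.3 and 17-32% at 0.6. Faculty (logit SD 1.0): about 6% and 25%.
- Second simulation, with log-count covariates: about 6% at 0.4 and 23% at 0.7.
- There is no gain if users do not differ (variance ratio 1.03).

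Taken together: roughly 5-10% at 0.3-0.4 and 10-30% at 0.6-0.7.

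**6. Who has a baseline.** In the six baseline months 662 of 904 users (73.2%) made no search, leaving 242. Of these, 161 are occasional searchers, who share 1,358 - 1,025 = 333 searches, about 2.1 each; the 81 heavier users average 1,025/81 = 12.7. The baseline term is informative mainly for the 81.

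**The case against.** The strongest reply is that the plan gives one clause for an exploratory question in a condensed article. It does not state the unit, the period or the exact comparison, and details may sit in an analysis plan not shown. Randomization makes an unadjusted comparison unbiased in expectation, so baseline adjustment is a matter of efficiency. The interventions also aim at low-frequency users, most of whom have no baseline pattern to adjust for.

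Much of this stands, and it rules out several stronger readings that a reader might infer:
- That the plan says it will use follow-up data only. It does not; this is an inference from the bare chi-squared test and its contrast with the two adjusted models.
- That Table 6 holds each user's own pattern. It is pooled over 81 users; only the account logs could supply individual patterns.
- That adjustment would cut variance by 1 - r², for example 16% to 49% at r = 0.4 to 0.7. That formula needs the correlation between observed shares, which the documents do not give. When r describes underlying preferences and accesses are few, the simulated gains are smaller.
- That each comparison rests on about 27 versus 26 postgraduates and 14 versus 14 faculty. These are halved baseline counts; who will contribute accesses during follow-up is unknown.

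What does not stand is that this is merely omitted detail. The article names a test, and that test can neither take a covariate nor, on counted accesses, allow for repeated use by the same person.

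**Conclusion.** The point holds as a fault in a stated secondary method. The larger part is the unit of analysis: if accesses are counted, the false-positive rate rises well above 5% for any appreciable difference between users (13% to 44% by the design-effect formula at ICC 0.05 to 0.30; higher in simulations with unequal users). The smaller part is the unused baseline: roughly 5-10% less variance at a within-user correlation of 0.3-0.4 and 10-30% at 0.6-0.7, and less if follow-up accesses come mainly from users without baseline searches.

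Both sizes rest on assumed between-user variation, within-user correlation and concentration of use, and on Table 6 counts persisting into follow-up. If the test were applied to one classification per user, the clustering part would fall away and only the unused baseline would remain. The question is exploratory, and the primary outcome and its baseline-adjusted model are untouched.

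**What to change.** In Analysis of secondary questions, replace the chi-squared test of access, and only that part of the sentence. The questionnaire comparison can keep its test, since each participant is followed only until one completed form is returned.

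Suggested content: within each trial, a user-level model of six-month accesses to summaries plus pre-appraised research versus non-pre-appraised research, on the three intervention dummies. Covariates are the same user's baseline accesses to each of the two groups, entered as log(count + 0.5), so that users with no baseline access stay in the model. Inference should be cluster-robust by user with a small-sample correction, or by permutation of the allocation within strata. State explicitly that a plain binomial model is not enough.

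The cost is one or two sentences and some programming. The baseline accesses are already logged, no new data are needed, and Trial status says that no analysis has begun, so the change can be made before results are seen.
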